### Secondary study parameters

changes in LBP intensity, PVAQ, HADS, EQ-5D, ODI, PGIC and painDETECT rates will be compared between groups using the independent-samples *t*-test. Group differences in subject satisfaction with treatment will be compared using the Mann-Whitney *U* test. The percentage of subjects who achieve a reduction inLBP intensity of ≥50% and 30% compared to baseline and the percentage of patients experiencing AE’s or SAE’s will be compared between groups using Pearson’s chi-squared test. In case of expected cell counts of 5 or lower, Fisher’s exact test will be used. Analgesia intake changes between the 2 groups and incidence of AE or SAEs will be assessed using descriptive statistics only.

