## Administrative information

**Table Taba:** 

Data category	Information
Primary registry and trial identifying number	Clinicaltrials.gov: NCT05421273, registered Netherlands Trial Register NL9194, registered
Date of registration in primary registry	23 January 2021
Secondary identifying numbers	n/a
Source(s) of monetary or material support	Abbott Laboratories
Primary sponsor	Abbott Laboratories
Secondary sponsor(s)	N/A
Contact for public queries	[name] [contact], [name] [contact]
Contact for scientific queries	[name] [contact], [name] [contact]
Public title	N/A
Scientific title	Effects of Active Versus Passive Recharge Burst Spinal Cord Stimulation on Pain Experience in Persistent Spinal Pain Syndrome Type 2: A Multicenter Randomized Trial (BURST-RAP study)
Countries of recruitment	The Netherlands
Health condition(s) or problem(s) studied	Persistent Spinal Pain Syndrome Type 2
Intervention(s)	Passive recharge burst (Burst DR^TM^) spinal cord stimulation
	Active recharge burst spinal cord stimulation
Key inclusion and exclusion criteria	Ages eligible for study: ≥18 years Sexes eligible for study: both
	Inclusion criteria Subjects between 18 and 65 years of age At least moderate level of catastrophizing as measured with the Pain catastrophizing scale (PCS) of at least 20. History consistent with PSPS Type 2 of at least 6 months
	Exclusion criteria Subject is unable to operate the device Severe spinal column degeneration likely to cause technical problems with neuromodulation, to be assessed by the treating physician
Study type	Investigator initiated multicenter randomized clinical trial
	Allocation: Unblinded randomization
	Primary purpose: Pain Experience
Date of first enrolment	February 2022
Target sample size	94
Recruitment status	Recruiting
Primary outcome(s)	Change on the PCS scale
Key secondary outcomes	Change in low back and leg pain intenstity, PVAQ, HADS, EQ-5D, ODI, PGIC, analgesia intake and PainDETECT rates

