## Background

Spinal cord stimulation (SCS) is increasingly being used for the treatment of patients with intractable chronic pain that are resistant to conventional treatment options [1]. SCS has been shown to reduce pain in patients with intractable chronic pain, improve quality of life and reduce use of analgesics, while maintaining a low rate of adverse effects [2]. The most common indication for spinal cord stimulation is persistent spinal pain syndrome type 2 (PSPS Type 2), previously referred to as failed back surgery syndrome (FBSS) [3–9]. PSPS Type 2 is marked by radicular neuropathic or neuroplastic leg or arm pain, sometimes combined with low back pain (LBP), resulting in a significant decline in their quality of life, psychological outlook and work productivity [3, 10–16].

Patients receiving conventional SCS, characterized by electrical pulses delivered in the 40–60Hz stimulation frequency range, experience paresthesia or a tingling sensations in the painful area. Burst SCS is a new stimulation paradigm that has been suggested to be even more effective compared to conventional SCS and is now approved worldwide [17]. Furthermore, burst SCS eliminates or greatly reduces the incidence of paresthesia [18], hinting at a different underlying mechanism of action as compared to conventional SCS [19]. Burst SCS consist of delivering groups of electrical pulses (also referred to as “burst trains”) which are repeated at a burst rate; within each burst train, several pulses are issued at an intra-burst rate [20]. Following each pulse a recharge pattern is required to prevent the buildup of charge in the stimulated tissue. Individual pulses are characterized by a pulse amplitude and pulse width.

Currently, two variations of burst-SCS are used in treatment of patients with intractable chronic pain. These two variations differ with respect to the recharge pattern employed in the burst train: on the one hand a burst paradigm employing passive recharge (referred to as BurstDR, developed by Abbott Laboratories [20, 21]) and on the other hand using an active recharge pattern (used by Boston Scientific [22–24]).

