### Inclusion criteria

Subjects between 18 and 70 years of age.At least moderate level of catastrophizing as measured with the Pain Catastrophizing Scale (PCS) of at least 20 at first visit of the pain clinic.Chronic pain diagnosed as PSPS Type 2 for at least 6 months.Neurologic exam without marked motor deficit.LBP and/or leg pain intensity should be 5 or higher measured with the 11-box NRS 0-10.Meets all the inclusion criteria for the implantation of a neurostimulation system as typically utilized in the study centre. Depression is not an exclusion criteria.Subject has been screened by a multi-disciplinary panel including a psychologist and deemed suitable for implantation.Subject is able and willing to comply with the follow-up schedule and protocol.Subject is able to provide written informed consent.

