### Study procedure

 Following inclusion and consent, patients are randomized into two groups: passive burst SCS or active burst SCS. Randomization is performed by local study staff using Castor study management software. Patients are stratified per group and per center for PCS rate (two groups of 20-35 and 35-52), gender and pain location.

Procedures in this study do not deviate from standard neuromodulation care for PSPS Type 2 patients. First, a trial period occurs where patients are implanted with either two Abbott Octrodes or two Boston Scientific Infinion leads in the dorsalepidural space; during the procedure paresthesia testing is performed to achieve maximum overlap with the pain area of the patient. During this trial period, patients are stimulated by an external pulse generator. Stimulation settings are set by clinical programmers provided by Abbott and Boston Scientific, who individually assess optimal burst stimulation parameters for every individual participating patient. Due to the subsequent nature of the study, patients cannot be blinded. Following a test phase of 2 weeks and a minimal pain reduction of 50%, patients are implanted with an internal IPG (Proclaim 5/XR (Abbott Laboratories) or Waverwriter Alpha (Boston Scientific)). When pain reduction is less than 50%, the trial is expanded by 1 week, and other (non-burst) waveforms possible with the implanted system can be tried, with the aim to induce pain relief. These patients, with at least 50% pain relief, will remain in the study and complete long-term follow up questionnaires.

Data regarding pain state and mental attitude towards pain are collected at baseline, after trial, 1 month, 3 months, 6 months and 12 months following implantation. Patients will electronically complete the Pain Catastrophizing Scale (PCS) [38], Numeric Pain Rating Scale (NRS), Patient Vigilance and Awareness Questionnaire (PVAQ) [40, 41], Hospital Anxiety and Depression Scale (HADS) [42, 43], Quality of Life (EQ-5D) [44–46], Oswestery Disability Index (ODI) [47], Patient Global Impression of Change (PGIC) [48] and painDETECT [49, 50] questionnaires using the CASTOR data collection system. Additionally, use of pain medication alongside neuromodulation is recorded at every follow-up contact, as well as the mean charge per second (CpS) and mean charge per hour (CpH) as used by the stimulation apparatus in order to gain insight into electrical consumption.

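### Leg pain is a listed key secondary outcome and qualifies patients on its own, but the analysis section gives it no analysis and defines pain responders on low back pain only

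*Protocol article*

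**What the plan says.** Four places in the protocol article bear on which pain site is measured and analysed.

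- **Administrative information, key secondary outcomes:** "Change in low back and leg pain intenstity, PVAQ, HADS, EQ-5D, ODI, PGIC, analgesia intake and PainDETECT rates".
- **Inclusion criteria:** "LBP and/or leg pain intensity should be 5 or higher measured with the 11-box NRS 0-10". The and/or means that leg pain alone is enough, whatever the low back score.
- **Study procedure:** "Patients are stratified per group and per center for PCS rate (two groups of 20-35 and 35-52), gender and pain location". The design therefore expects patients to differ in pain location.
- **Secondary study parameters:** "changes in LBP intensity, PVAQ, HADS, EQ-5D, ODI, PGIC and painDETECT rates will be compared between groups" by independent-samples t-test. The responder endpoint is "The percentage of subjects who achieve a reduction inLBP intensity of ≥50% and 30% compared to baseline", compared by chi-squared or Fisher's exact test.

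The Background describes the condition as "radicular neuropathic or neuroplastic leg or arm pain, sometimes combined with low back pain (LBP", so limb pain is the defining feature and low back pain an addition in some patients.

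**The concern.** The outcome list and the analysis paragraph do not match. The paragraph repeats the list almost item for item, but where the list has low back and leg pain, the paragraph has only low back pain. Since the article itself fixes these analyses, this is a conflict between two of its statements rather than detail left for later.

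The eligibility rule makes the mismatch matter. The stated objective includes comparing the two waveforms on pain relief, without limiting it to the back. In a patient implanted for leg pain with little or no back pain, an LBP endpoint does not record whether the treated pain improved. A difference between waveforms in leg pain would not appear in any analysis the article names. The responder rate would mix relief of the qualifying pain with movement in a minor or absent pain.

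**Working it through.** **1. Outcome list against stated analysis.**

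| Key secondary outcome listed | Analysis in Secondary study parameters |
|---|---|
| Low back pain intensity | t-test; 50% and 30% responders |
| Leg pain intensity | none stated |
| PVAQ, HADS, EQ-5D, ODI, PGIC, painDETECT | t-test |
| Analgesia intake | descriptive |

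Leg pain is the only listed item left without an analysis.

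**2. The responder definition in patients who qualify on leg pain.** Percentage reduction = (baseline − follow-up) / baseline × 100, on the 0–10 NRS in whole points.

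| Baseline LBP | Smallest drop for 30% | Smallest drop for 50% |
|---|---|---|
| 0 | undefined (division by 0) | undefined |
| 1 | 1 point (100%) | 1 point (100%) |
| 2 | 1 point (50%) | 1 point (50%) |
| 3 | 1 point (33%) | 2 points (67%) |
| 4 | 2 points (50%) | 2 points (50%) |
| 5 (threshold) | 2 points (40%) | 3 points (60%) |

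The inclusion criteria allow every row from 0 to 4 if leg pain is 5 or more. At baseline LBP of 2, a single-point move makes a patient a 50% responder.

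**3. The t-test on LBP change.** This is computable for every patient with scores, including those at baseline 0. However, improvement cannot exceed the baseline score, so patients with little back pain can show little or none. If a share s of patients has no between-arm difference in LBP, a true difference D in the rest appears as (1 − s) × D overall.

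**4. Possible size, as illustration only.** The documents give neither the share of patients without meaningful LBP nor any pain responder rate. Assume responder rates of 60% and 30%, 47 patients per group (the planned number), two-sided 5%, and

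power = Φ{ [ |p1 − p2| − 1.96 √(2p̄(1 − p̄)/n) ] / √([p1(1 − p1) + p2(1 − p2)]/n) }, where p̄ is the mean of p1 and p2.

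With everyone contributing: (0.30 − 1.96 × 0.1026) / 0.0979 = 1.01, so power is 84%.

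| Assumed leg-only share | Left out: n per group, power | Counted as non-responders: rates, power |
|---|---|---|
| 10% | 42.3, 80% | 54% v 27%, 77% |
| 20% | 37.6, 75% | 48% v 24%, 68% |
| 30% | 32.9, 69% | 42% v 21%, 59% |

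Under these assumptions power falls as the share rises. The amounts depend wholly on the assumptions and are not estimates for this trial.

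**5. The sample size is not touched.** It rests on the PCS: 2 × [12.04 × (1.645 + 0.842) / 7]² = 36.6, so 37 per group and 74 in total. Then 74 / 0.8 = 92.5, which the article rounds to 94. This reproduces the stated figures, and no pain score enters it.

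**The case against.** The strongest reply is that the text mismatch is real but its consequences are easily exaggerated. Several stronger readings are tempting and the documents do not support them.

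- **That leg-pain patients cannot contribute a valid response.** This is strictly true only at a baseline LBP of exactly 0, and only for the percentage responder endpoint. The t-test on change is computable for all. Nothing shows how many enrolled patients, if any, have a score of 0.
- **That everyone with predominant leg pain is affected.** Leg-dominant is not leg-only. A patient with leg pain of 8 and LBP of 6 meets the threshold at both sites and gives an informative LBP response. An assumed leg-dominant share multiplied by 94 would not count the affected patients.
- **That the comparison is biased.** Randomization is stratified by pain location, so such patients should be roughly balanced between arms. The harm is dilution and lost information.
- **That leg pain will go unanalysed in the trial.** The article condenses a longer protocol, and an analysis plan may exist. What can be said is that the article's analysis section omits it.

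All four limits stand. It is also fair to say that the scoring of a baseline of 0 is detail often settled in an analysis plan. That does not remove the point: the article fixes both the outcome list and the analyses, the two disagree, and the responder definition it fixes does not fit patients whom its own criteria admit.

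**Conclusion.** The point holds in limited form. The article lists leg pain change as a key secondary, admits patients on leg pain alone, assigns leg pain no analysis and defines responders on LBP only. For some eligible patients responder status is undefined (baseline LBP of 0) or does not reflect the qualifying pain (baseline LBP of 1 to 4). That weakens the answer to the trial's own pain-relief question.

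The omission is certain from the text. Its size is not: the share of affected patients is not given, and the power figures above show direction only, under assumed rates. Only secondary endpoints are involved. The primary PCS comparison, its non-inferiority conclusion and the sample size do not change. The change is worth making before outcome data are analysed, because how to score these patients should not be decided after the results are seen in a trial without patient blinding.

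**What to change.** In Secondary study parameters:

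1. Name leg pain NRS change next to LBP change, with its own between-group comparison.
2. Define the 50% and 30% responders in one of two ways: on the qualifying pain site (baseline NRS of 5 or more), stating the rule when both sites qualify; or separately for LBP and leg pain, each among patients with baseline NRS of 5 or more at that site. Either resolves the problem. The second avoids a mixed-site endpoint.
3. Take account of the pain-location stratum in these comparisons.

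The cost is wording and one more secondary outcome to report. The NRS is already scheduled at baseline and every follow-up, and both sites are named in the eligibility rule and the outcome list. The article does not say outright that the two sites are scored separately at each visit, so this should be confirmed.

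A separate minor point in the same paragraph: the percentage of patients with adverse events or serious adverse events is to be compared by chi-squared or Fisher's exact test, yet "incidence of AE or SAEs will be assessed using descriptive statistics only". The two may refer to patients and to event counts, but the text does not say so. State whether the percentages are tested or only described.

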**Methods:**

This multicentre randomized clinical trial will take place in 6 Dutch hospitals. PSPS Type 2 patients (*n=94*) will be randomized into a group receiving either active or passive recharge burst. Following a successful trial period, patients are permanently implanted. Patients complete the Pain Catastrophizing Scale (PCS) (primary outcome at 6 months), Numeric Pain Rating Scale (NRS), Patient Vigilance and Awareness Questionnaire (PVAQ), Hospital Anxiety and Depression Scale (HADS), Quality of Life (EQ-5D), Oswestery Disability Index (ODI), Patient Global Impression of Change (PGIC) and painDETECT questionnaires (secondary outcomes) at baseline, after trial, 1, 3, 6 and 12 months following implantation.

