### Sample size calculation

This study follows a non-inferiority setup based on the primary outcome measure, the PCS. The non-inferiority limit of 7 points on the PCS scale (13.46%) was defined based on an estimation of the clinically meaningful score of PCS scores established on experience with this test at the main research centre. Previous literature investigating the clinically meaningful difference of the PCS scale estimates that this lies at around 44% [51]. However, as this study was performed in patients with subacute pain after whiplash injury, the decision was made to lower the non-inferiority limit for patients with PSPS Type 2, a chronic debilitating condition with neuropathic components.

In order to calculate group size, an estimation of the expected standard deviation (SD) was based on previous literature for FBSS patients with neuromodulation to be 12.04 points on the PCS scale [4]. In combination with a non-inferiority limit of 7 points, 80% power and 5% significance level, this results in a group size of 37 patients per group or 74 patients total. Compensating for a drop-out rate of 20% (including failed initial trials), we arrive at 92.5 patients. However, this is rounded to 94 patients in order to ensure even group size of 47 patients per group.

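### PGIC, already a rating of change, is scheduled at enrolment and listed among outcomes analysed as changes; the follow-up rating should be compared directly

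*Protocol article*

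**What the plan says.** Five places in the protocol article bear on PGIC.

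- **Secondary study parameters:** "changes in LBP intensity, PVAQ, HADS, EQ-5D, ODI, PGIC and painDETECT rates will be compared between groups using the independent-samples" *t*-test. No other analysis of PGIC is given.
- **Administrative information table, key secondary outcomes:** "Change in low back and leg pain intenstity, PVAQ, HADS, EQ-5D, ODI, PGIC, analgesia intake and PainDETECT rates". PGIC again stands behind the word change.
- **Abstract, methods:** "Patient Global Impression of Change (PGIC) and painDETECT questionnaires (secondary outcomes) at baseline, after trial, 1, 3, 6 and 12 months following implantation".
- **Study procedure:** "Data regarding pain state and mental attitude towards pain are collected at baseline, after trial, 1 month, 3 months, 6 months and 12 months following" (the visits are counted from the implant). The questionnaires then listed include "Patient Global Impression of Change (PGIC) [48] and painDETECT [49, 50] questionnaires using the CASTOR data collection system", which spells out what PGIC stands for.
- **Table 1:** the PGIC row has an X under Enrolment, none under Implantation, and an X at every later column.

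The secondary-parameters section treats another patient rating differently: "Group differences in subject satisfaction with treatment will be compared using the Mann-Whitney" *U* test. Satisfaction is compared directly between groups, with no mention of change.

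**The concern.** The other instruments in the *t*-test list (low back pain intensity, PVAQ, HADS, EQ-5D, ODI, painDETECT) can be scored before treatment, so a change from baseline is well defined for each. PGIC, by its name, records the patient's impression of how things have changed. Before stimulation there is no treatment-related change to rate. If an enrolment PGIC is subtracted from a later one, the result is a difference between two change ratings, and its mean has no ready clinical reading.

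Two things are at stake for this named secondary outcome. The first is interpretation. The second is precision, because scatter in the enrolment ratings that has nothing to do with follow-up goes straight into the outcome. There is also a smaller issue of pre-specification: patients are not blinded, and the wording leaves room to choose later between the raw rating and the subtracted one.

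**Working it through.** **The plan's own figure.** The only sample size stated is for PCS. The inputs, from the sample size section, are a margin of 7 points, an SD stated "to be 12.04 points on the PCS scale", 80% power and a 5% level, taken as one-sided because the primary analysis uses a one-sided 95% interval.

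n per group = 2 × (1.645 + 0.842)² × (12.04/7)² = 2 × 6.18 × 2.958 = 36.6, rounded up to 37. Then 74/0.80 = 92.5, which the plan rounds to 94. The figure reproduces. It does not depend on PGIC, and no figure is stated for PGIC.

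**Reading the places together.** The *t*-test sentence does not itself say from enrolment. A change in a score needs a reference value, though, and the schedule supplies one at enrolment. The administrative table repeats the change wording. Nothing in the article gives PGIC a different analysis.

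**Effect on precision.** Let the follow-up PGIC have SD s, the enrolment PGIC SD ks, and let their correlation be ρ. Then

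Var(follow-up − enrolment) = s²(1 + k² − 2ρk).

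With ρ = 0 the effective sample is multiplied by 1/(1 + k²), and the detectable difference by √(1 + k²). For 37 per arm, two-sided 5% and 80% power, the detectable difference without subtraction is 0.660 SD (noncentral *t*). The values of k and ρ are assumptions; so is the two-sided 5% level for this test, and 37 per arm is borrowed from the PCS calculation.

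| k (ρ = 0) | Effective sample | Detectable difference, in follow-up SDs |
|---|---|---|
| 0 (all enrolment ratings are no change) | 100% | 0.660 |
| 0.5 | 1/1.25 = 80% | 0.660 × 1.118 = 0.738 |
| 1 | 1/2 = 50% | 0.660 × 1.414 = 0.934 |

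Correlation reduces the loss. It vanishes when ρ = k/2, for example at k = 1 and ρ = 0.5, since 1 + 1 − 1 = 1.

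**Simulation check.** This used 10,000 runs, 37 per arm and an assumed seven-category PGIC. Follow-up probabilities for categories 1 to 7 were 0.05, 0.05, 0.10, 0.15, 0.20, 0.25, 0.20 in one arm and 0.08, 0.09, 0.15, 0.20, 0.20, 0.18, 0.10 in the other. Enrolment ratings were either all in the middle category, or spread as 0.15, 0.20, 0.20, 0.30, 0.10, 0.03, 0.02 independently of follow-up. The spread case has enrolment variance 2.06 against an average follow-up variance of (2.85 + 2.97)/2 = 2.91, so k = √(2.06/2.91) ≈ 0.84.

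| Enrolment ratings | *t*-test on difference | *t*-test on follow-up | Mann-Whitney on follow-up |
|---|---|---|---|
| All no change: power | 38.5% | 38.5% | 40.2% |
| Spread: power | 23.3% | 37.1% | 39.0% |

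With no true difference, every method rejected in 4.9% to 5.1% of runs. The precision loss comes from the subtraction. The choice between *t*-test and rank test moves power by less than 2 percentage points.

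**The case against.** The strongest defence is that the sentence is compressed drafting. One phrase governs seven instruments, PGIC is itself a change measure, and an explicit comparison with baseline appears in that section only for the low back pain responder percentages. The authors may intend to compare the follow-up rating and ignore the enrolment one. This stands in part: the subtraction is an inference, not a stated step. Against it, the administrative table repeats the change wording, and the abstract, study procedure and Table 1 all supply a baseline value, so the inference is the natural one.

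The documents do not support several stronger readings.

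- A reader might infer that the comparison has no valid meaning. It does not go that far: randomisation protects the type I error, and if all enrolment ratings equal no change, the test is the same as a test on follow-up PGIC.
- A reader might call the *t*-test itself a fault because PGIC is ordinal. The article describes the response scale of neither PGIC nor the satisfaction item, so the ordinal scale is an assumption from the type of instrument, and the gain from a rank test is small.
- A reader might expect patients without an enrolment rating to be lost from the comparison. The article states no missing-data rule for secondary outcomes, so this is conjecture.
- The losses at k = 0.5 and k = 1 are illustrations. Before stimulation, no change is a natural answer, and k near zero is at least as plausible.

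**Conclusion.** The point holds as one of interpretability and possible loss of precision in a secondary outcome. As written, the plan handles a rating of change like a state scale with a baseline. The difficulty of interpretation applies whatever the enrolment ratings turn out to be. The loss of precision depends on them: none if they are constant, 20% of the effective sample if their SD is half the follow-up SD and they are uncorrelated with follow-up, and less where the two ratings correlate positively. Type I error, the PCS non-inferiority analysis and the sample size are not affected. The conclusion rests on reading the analysis sentence together with the schedule, and on PGIC measuring what its name says.

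**What to change.** 1. In the secondary study parameters section and in the key secondary outcomes of the administrative table, take PGIC out of the outcomes introduced as changes.
2. Add one sentence: the follow-up PGIC rating is compared directly between arms at a named visit, for example 6 months to match the primary outcome, preferably with the Mann-Whitney *U* test already planned for satisfaction. A proportional-odds model would also serve.
3. Remove the enrolment X for PGIC from Table 1, and exclude PGIC from the baseline collection described in the abstract and study procedure. The first patient was included in February 2022, so some enrolment ratings may already exist; state that these are not used in the analysis.

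The cost is one added sentence, small wording edits, one table cell and one fewer questionnaire at enrolment. No extra patients are needed, and the target of 94 stands.

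### Analgesia intake is a listed key secondary outcome but gets summaries by arm only; add a between-arm difference with a 95% confidence interval

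*Protocol article*

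**What the plan says.** The Administrative information table of the protocol article gives the key secondary outcomes as "Change in low back and leg pain intenstity, PVAQ, HADS, EQ-5D, ODI, PGIC, analgesia intake and PainDETECT rates". Analgesia intake stands there on the same footing as the questionnaires.

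Under Study procedure, "use of pain medication alongside neuromodulation is recorded at every follow-up contact". The same section states that "Procedures in this study do not deviate from standard neuromodulation care for PSPS Type 2 patients" and that "Due to the subsequent nature of the study, patients cannot be blinded". Under Sample size calculation, "This study follows a non-inferiority setup based on the primary outcome measure, the PCS".

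Secondary study parameters then sets the methods. For most outcomes, "changes in LBP intensity, PVAQ, HADS, EQ-5D, ODI, PGIC and painDETECT rates will be compared between groups using the independent-samples *t*-test". Treatment satisfaction gets a Mann-Whitney test, and the 30% and 50% pain responders get a chi-squared or Fisher test. For medication, the text is: "Analgesia intake changes between the 2 groups and incidence of AE or SAEs will be assessed using descriptive statistics only".

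**The concern.** Analgesia intake is singled out. Of the key secondary outcomes in the table that the methods section also names, it is the only one without a between-group comparison, and no reason is given. Low power does not explain this, because the sample size was set for the PCS and none of the secondary outcomes was powered. Skewed data do not explain it either, because the section already uses a rank method for satisfaction.

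The outcome matters more here than in a blinded superiority trial. Patients know their device, and pain medication can be adjusted alongside stimulation. If one arm took more of it, PCS and pain scores in the two arms could move closer together. A reader who sees a non-inferior PCS result will therefore ask whether medication use was similar. Two sets of summaries side by side give a rough answer. They do not say how large a difference the data are compatible with.

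**Working it through.** **Step 1. Is this a stated choice or an omission?** The table names the outcome, Study procedure collects it, and the methods section limits it to description with the word *only*. That is a fixed method, not detail left to a statistical analysis plan. A later plan could add an interval only by departing from this sentence.

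**Step 2. Reproduce the plan's sample size.** Inputs from Sample size calculation: standard deviation (SD) 12.04, margin 7, power 80%, significance level 5% (taken as one-sided, to match the one-sided 95% interval under Primary study parameters), drop-out 20%.

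- n per arm = 2 × 12.04² × (1.645 + 0.842)² / 7² = 2 × 144.96 × 6.185 / 49 = 36.6, rounded up to 37.
- 74 / 0.80 = 92.5, which the plan rounds to 94, or 47 per arm.

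The plan's figures reproduce. They fix the range of patients available for analgesia: 37 per arm after the assumed drop-out, 47 per arm if everyone contributes.

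**Step 3. Precision of a between-arm difference in intake.** The documents give no SD for analgesia intake, so the result is in SD units. It uses the normal approximation for a difference in means. A Hodges-Lehmann or bootstrap interval on skewed data will differ somewhat.

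Half-width of the two-sided 95% interval = 1.96 × √(2/n):

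- n = 37: 1.96 × 0.2325 = 0.46 SD
- n = 47: 1.96 × 0.2063 = 0.40 SD

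**Step 4. What a significance test would add.** The difference detectable with 80% power at two-sided 5% = (1.96 + 0.842) × √(2/n):

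- n = 37: 2.802 × 0.2325 = 0.65 SD
- n = 47: 2.802 × 0.2063 = 0.58 SD

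Power at smaller true differences:

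| True difference | 37 per arm | 47 per arm |
|---|---|---|
| 0.2 SD | 14% | 16% |
| 0.3 SD | 25% | 31% |
| 0.5 SD | 58% | 68% |

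A non-significant p-value would therefore say little. An interval shows which imbalances remain possible.

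**Step 5. Precision for the percentage taking any opioid.** The documents give no percentage. Assuming 50% in each arm, where the variance is greatest, the half-width = 1.96 × √(2 × 0.5 × 0.5 / n):

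- n = 37: 1.96 × 0.1162 = 0.23, or 23 percentage points
- n = 47: 1.96 × 0.1031 = 0.20, or 20 percentage points

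At percentages further from 50% the interval is narrower.

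**The case against.** The strongest reply is that nothing here is wrong. Listing an outcome as secondary does not promise a test, and describing an unpowered outcome is a legitimate choice. The interval would be wide, so it could not rule out a modest imbalance. All of this stands, and it is why the point is only an improvement. It does not remove the case for an interval, because a wide interval shows how little the data can exclude, and summaries by arm do not.

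A reader might infer several stronger points. The document does not support them.

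- *The trial cannot tell whether similar scores were reached with more medication.* Intake is collected throughout follow-up and described by arm, so a large imbalance would be visible.
- *Analgesics are unrestricted.* The article describes no restriction, but it is a condensed text that refers to standard care. The full protocol may contain medication rules.
- *Extra medication inflates the risk of a false non-inferiority claim by a calculable amount.* Any such figure needs an assumed effect of medication on the PCS, and the document gives none. It would also be the same whether intake is reported with or without an interval. It further presupposes a treatment effect with medication held equal, whereas the article states intention-to-treat analysis under standard care and even permits a switch of waveform. If the question is how each strategy performs in practice, medication changes may be part of the strategy.
- *Responders whose intake rose should be recoded as failures.* The responder outcomes are clearly defined on pain intensity. Recoding would create a new composite, which is a debatable preference.

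**Conclusion.** The point holds as a modest one. The plan names analgesia intake as a key secondary outcome and collects it. It then rules out a between-arm estimate with uncertainty, while comparing the other listed outcomes that it names. In an unblinded non-inferiority trial, that estimate would help in reading the PCS result.

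The size of the issue is the missing interval. With the planned numbers, its half-width would be about 0.40 to 0.46 SD for intake, and about 20 to 23 percentage points for opioid use if half the patients take opioids. These figures assume 37 to 47 patients per arm and a normal approximation. The primary analysis and the sample size are unaffected. The document gives no evidence that medication use will differ between the arms.

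**What to change.** In Secondary study parameters, separate analgesia intake from the sentence on adverse events and replace the restriction to description with the following:

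- the between-arm difference in analgesia intake at 6 months, with a two-sided 95% confidence interval by a method suited to skewed data (for example Hodges-Lehmann or bootstrap), on a daily equivalent specified before the data are analysed;
- the difference between arms in the percentage taking any opioid at 6 months, with its 95% confidence interval;
- a statement that both are supportive and are read alongside the PCS result, and that an interval including zero does not show equal use.

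Six months is the natural time point, because it matches the primary outcome and comes before the scheduled open-label phase.

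The cost is wording, the choice of a dose-equivalence conversion, and coding of medication data already collected. That choice involves judgement, so it should be fixed before analysis. No extra visits or patients are needed and no clinical rule changes. The downside is a wide interval that may not settle the question.
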